### The intervention

The Nutritional Intervention Preconception and During Pregnancy to Maintain Healthy Glucose Metabolism and Offspring Health (NiPPeR) intervention comprises: (1) a micronutrient-enriched nutritional drink containing myo-inositol, vitamin D, riboflavin, vitamin B_6_, vitamin B_12_ and zinc together with standard folic acid, iodine, calcium, β-carotene and iron; the quantities proposed are either standard amounts (myo-inositol [54]), enhanced amounts that are available in over-the-counter products (vitamins B_6_, B_12_, riboflavin), recommended daily allowance amounts in UK for pregnant women (vitamin D, zinc, folic acid, iodine) or minimal amounts for micronutrients linked with potential detrimental effects at higher doses (iron, β-carotene, calcium) and (2) probiotics (containing *Lactobacillus rhamnosus* NCC 4007 (CGMCC 1.3724) also known as LPR and *Bifidobacterium animalis* sp. *lactis* NCC 2818 (CNCM I-3446) also known as Bl818) [52]. The intervention group will be compared with a control group who receive a drink containing standard amounts of micronutrients that are part of routine pregnancy care (including folic acid, β-carotene, iron, calcium and iodine). The intervention is formulated as a powder in sachets to be made up in water immediately prior to consumption, with similar sensory characteristics for both the intervention and control drinks. The constituents of the intervention and control drinks are shown in Table 1, including the rationale for the amounts included. This trial uses established nutritional elements for which tolerability is well established. Confirmation that the trial is not a Clinical Trial of an Investigational Medicinal Product has been secured from MedSafe (New Zealand), Medicines and Healthcare products Regulatory Agency, MHRA (UK) and the Health Sciences Authority (Singapore).

**Table 1 Tab1:** Constituents of the intervention and control drinks

Intervention group	Daily amount	Rationale
Myo-inositol	4 g	Improves glucose metabolism and preliminary data suggest may maintain healthy glucose metabolism in pregnancy; dose safely used in pregnancy
Vitamin D_3_	400 IU	Deficiency highly prevalent and linked with glucose metabolism in pregnancy and offspring postnatal adiposity gain; dose sufficient to reduce insufficiency while avoiding potential concerns re adverse effects at high doses. Omission from control group supported by a *Lancet* study [56]
Vitamin B_6_	2.6 mg	Deficiency highly prevalent and linked with glucose metabolism in pregnancy and offspring postnatal adiposity gain [33]; dose sufficient to rectify deficiency and present in current over-the-counter products (e.g. Elevit). Omission from control group supported by usual clinical practice
Vitamin B_12_	5.2 μg	Deficiency highly prevalent and linked with glucose metabolism in pregnancy and offspring postnatal adiposity gain; dose sufficient to rectify deficiency and less than that in current over-the-counter products (e.g. Elevit). Omission from control group supported by usual clinical practice
Riboflavin	1.8 mg	Low intake highly prevalent and linked with offspring postnatal adiposity gain [34]; dose sufficient to rectify deficiency and present in current over-the-counter products (e.g. Elevit). Omission from control group supported by usual clinical practice
Zinc	10 mg	Deficiency highly prevalent and linked with offspring postnatal adiposity gain [unpublished]; dose sufficient to rectify deficiency and present in current over-the-counter products (e.g. Elevit). Omission from control group supported by usual clinical practice
β-carotene	720 μg (15% of vitamin A requirements, as retinol equivalents)	Required in pregnancy in some jurisdictions
Folic acid	400 μg	Standard preconception recommendation
Iron	12 mg	Iron is routinely prescribed and taken before/during pregnancy, though without convincing evidence of benefit; low dose included to lessen likelihood of additionally receiving a high-dose iron product, which has been linked with glucose metabolism in pregnancy
Calcium	150 mg	A low dose of calcium is commonly taken before/during pregnancy; provision of this will lessen the likelihood of additional products being taken
Iodine	150 μg	Standard preconception recommendation
Probiotic		Taking a combination of two probiotics has been linked with maintenance of healthy glucose metabolism in pregnancy. Probiotic capsule containing >1 × 10^9^ cfu each of *Lactobacillus rhamnosus* NCC 4007 (CGMCC 1.3724) also known as LPR and *Bifidobacterium animalis* sp. *lactis* NCC 2818 (CNCM I-3446) also known as Bl818
Control group		
Folic acid	400 μg	Standard preconception recommendation
Iron	12 mg	Iron is routinely prescribed and taken before/during pregnancy, though without convincing evidence of benefit; low dose included to lessen likelihood of additionally receiving a high-dose iron product, which has been linked with glucose metabolism in pregnancy
Calcium	150 mg	A low dose of calcium is commonly taken before/during pregnancy; provision of this will lessen the likelihood of additional products being taken
Iodine	150 μg	Standard preconception recommendation http://www.cdc.gov/preconception/documents/clinical-content_womensnutritionfactsheet3.pdf
β-carotene	720 μg (15% of vitamin A requirements, as retinol equivalents)	Required in pregnancy in some jurisdictions

### Outcome measurements

The primary analysis will adjust for site, ethnicity and preconception glycaemia to account for potential imbalance between treatment arms amongst pregnancies which reach 28 weeks’ gestation, examining for differences in means between the control and intervention groups for the primary endpoint, specifically the fasting and/or 60-min and/or 2-h glucose concentrations following a 75-g OGTT at 28 weeks’ gestation. Maternal glucose metabolism at 28 weeks’ gestation has been chosen as the primary outcome as there is evidence that maintaining normal carbohydrate metabolism during pregnancy is associated with a healthier body composition, a reduced risk of obesity and potentially promotion of allergic/respiratory health in the children [55], alongside the recognised pregnancy benefits for the mother.

Secondary maternal outcomes of the initial phase of the NiPPeR study are:Maintenance of a healthy pregnancy, including normal duration of gestation (at least 37 weeks’ gestation), absence of GDM (defined using the International Association of the Diabetes and Pregnancy Study Groups criteria: glucose cut-off values of ≥5.1 mmol/L for fasting plasma glucose, and/or ≥10.0 mmol/L for 1-h and/or ≥8.5 mmol/L for 2-h post load), change in fasting glucose and OGTT glucose area under the curve from preconception baseline to 28 weeks’ gestation, maternal wellbeing/mood, absence of excessive nausea and vomiting, adequate pregnancy weight gain (Institute of Medicine criteria) and vaginal delivery ratesReduction in maternal micronutrient insufficiency, specifically less riboflavin, vitamin B_6_, vitamin B_12_, zinc and vitamin D insufficiency, before and during pregnancyAlteration in gut microbiota consistent with enhanced wellbeingAlteration in maternal metabolomic and epigenetic biomarkers consistent with improved maternal and/or offspring wellbeingEnhancement of breast milk micronutrient content, altered immunological factors, epigenetic and metabolomic profiles (subsample) and maintenance of healthy lactogenesis

Secondary offspring outcomes of the initial phase of the NiPPeR study are:Neonatal adiposity measured by PEA PODBirthweight 2500–4000 g, size for gestational age at birth and customised birthweight centileReduced adiposity gain during infancy, analysed taking account of infant feedingReduction in cord blood C-peptide as a marker of overall glycaemia during gestationPromotion of offspring wellbeing and healthy cardiometabolic risk factors, including visceral adiposity and markers of insulin resistance, during infancyAlteration in offspring metabolomic and epigenetic biomarkers in perinatal samples, consistent with improved infant metabolic and allergic wellbeingAlteration in gut microbiota to a microbiota associated with infant metabolic and allergic wellbeing

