Pregnancy represents a state of relative maternal insulin resistance, which helps to promote the transfer of nutrients, such as glucose, fatty acids and amino acids, to the fetus [16]. Placental nutrient transfer is determined by the concentration gradient, blood flow and the operation of active and facilitated transporters [17]. However, in contrast to amino acids, there is no upper limit to placental transfer of glucose and consequent fetal adipose accretion as maternal blood glucose levels rise [13]; this may be viewed as adaptive, as, in the neonatal period, relative adiposity provides metabolic reserves for thermogenesis and critical organs in the event of inadequate maternal care [18]. However, excessive materno-placental glucose transfer is associated with fetal hyperinsulinemia and macrosomia [19, 20] and an increased risk of fatal obstructed labour, suggesting that the levels of glucose exposure of the fetus that are often now experienced are novel in evolutionary terms [21].

Gestational diabetes mellitus (GDM) can be envisaged as the more extreme outcome of physiological processes, when maternal insulin resistance is accentuated by the woman’s own developmental, genetic and environmental circumstances: for example, women who themselves had a lower birth weight [22] or carry genetic variants associated with type-2 diabetes [23, 24] are at increased risk of GDM. Established risk factors for developing GDM include prepregnancy obesity [25], excessive gestational weight gain [26], advanced maternal age [27] and a previous pregnancy with GDM [28]. These factors are now increasingly common in women during their reproductive years with the evolutionary mismatched situation of over-nutrition and low levels of physical activity contributing not only to the rise in GDM but to the increasing prevalence of obesity and diabetes in their children, perpetuating a vicious cycle of disease. Such changes in growth potential and metabolic status may be mediated by inheritable epigenetic alterations occurring in utero [29]. For example, in Canadian first nation peoples, up to 30% of the incidence of type-2 diabetes has its origin in GDM in the previous generation [30]. Higher blood glucose levels in pregnancy carry risk of cardiovascular disease for both the mother as well as the child, a risk which increases with each pregnancy [31].

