The flow of the trial is shown in the Standard Protocol Items: Recommendations for Interventional Trials (SPIRIT) Figure (Fig. 1). See Additional file 1 for the SPIRIT checklist. Extensive biosampling and detailed phenotyping are embedded in the study with longitudinal assessments at multiple time points starting from the preconception phase throughout pregnancy and into the first year post delivery. The biosampling and phenotyping will enable detailed mechanistic insights and characterisation of potential new interventions for investigation in future studies. Following informed consent at the first preconception visit, a baseline standard 75-g oral glucose tolerance test (OGTT) will be conducted, nutritional status, lifestyle, mood, body anthropometry and metabolic phenotype ascertained and biosampling undertaken, followed by randomisation to the intervention or control drink. At the second preconception visit a month later, further biosampling will be undertaken and body composition assessed by DXA (dual-energy X-ray absorptiometry) scanning. Regular in-person and phone contact will be made with participants to resupply control/intervention drinks, and to encourage retention and compliance during the preconception phase. Participants who become pregnant within a year of commencing the intervention or control drink will be seen around 7, 12, 20, 28 and 34 weeks of pregnancy for further phenotyping, biosampling and ultrasound scans assessing fetal growth and development. At 28 weeks’ gestation, a standard 75-g OGTT will be repeated to ascertain the primary outcome. Normal antenatal care will be permitted during the trial. The fathers will be interviewed to ascertain paternal lifestyle and mood, their anthropometry measured and paternal biosamples collected. At birth, offspring cord blood, umbilical cord and placental samples will be collected. Neonatal body composition is assessed by anthropometry, air displacement plethysmography (PEA POD) and, in a subsample, by DXA scanning. Both breast- and formula-fed infants will be followed up when the infant is aged 1, 3 and 6 weeks, and 3, 6 and 12 months; infant feeding will be assessed in detail, biosamples collected and growth and wellbeing ascertained. Breast milk samples will be collected from a subset of participants in early infancy for nutrient and metabolic analysis. A maternal OGTT will be repeated again at 6 months postpartum and repeat biosamples collected. The site visits will be completed at the research and hospital facilities of the three sites in Auckland (University of Auckland, Auckland, Waitemata and Counties Manukau District Health Boards and Clinics, New Zealand), Singapore (National University Hospital and National University Health System Investigational Medicine Unit) and Southampton (National Institute for Health Research Wellcome Trust Southampton Clinical Research Facility and Princess Anne Hospital, University Hospital Southampton, UK).

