### Randomisation procedure

At preconception clinic visit 1 all eligible participants will be randomised via the electronic study database to either the nutritional drink or the control drink. This database will assign each participant the appropriate code number that is consistent with either the intervention nutritional drink arm or the control drink arm. Randomisation will be stratified by site to ensure balanced allocation of participants across the two arms at each of the three sites, with further stratification by ethnicity. Investigational products will be blinded by the manufacturer with nonspeaking codes that do not allow deduction of the identity of intervention or control drinks. Investigators, staff performing the assessments and data analysts will remain blind to the identity of the allocation from the time of randomisation until either the participant is unblinded or database lock of the primary outcome occurs. If emergency unblinding is necessary, the process for this will be documented in the study Safety Monitoring Plan.

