### Power calculations

By studying up to 900 prepregnant participants in each of the intervention and control groups, a total of 600 pregnancies and 500 live births is conservatively anticipated, following attrition from miscarriage, ectopic pregnancy, perinatal demise, multiple pregnancy, voluntary participant withdrawal, inability to comply with the protocol, withdrawal for medical reasons at the discretion of the investigator and loss-to-follow-up. A study of 250 pregnancies with 28-week OGTT data in each group has 89% power to detect a 0.1-mmol/L reduction in fasting plasma glucose and 84% power to detect a 0.3-mmol/L reduction in 2-h plasma glucose at the 5% level of significance. In the Hyperglycemia and Adverse Pregnancy Outcomes (HAPO) study such changes in glucose concentrations were associated with >10% changes in the odds of macrosomia and sum of neonatal skinfolds >90th centile and with a >20% change in cord C-peptide >90th centile [6]. As a further illustration of statistical power, using the distribution of 60-min plasma glucose in the HAPO study, a study of 250 participants in each of the two groups has 80% power to detect a difference of ≥0.43 mmol/L in 60-min glucose at *P* < 0.05. A study of 300 pregnancies in each arm will have an 80% power to detect a reduction in the mean plasma glucose of 0.12, 0.45 and 0.34 mmol/L at fasting, 60 min and 2 h, respectively, with an alpha of 0.017 taking into account multiple testing.

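### The primary model is defensible but leaves out preconception BMI, age and previous GDM, so imbalance in these named risk factors among the women analysed is only partly corrected and a little precision is forgone

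*Protocol article*

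**What the plan says.** The Outcome measurements section states the covariates and their purpose together: "The primary analysis will adjust for site, ethnicity and preconception glycaemia to account for potential imbalance between treatment arms amongst pregnancies" reaching 28 weeks' gestation. The contrast is a difference in means for "specifically the fasting and/or 60-min and/or 2-h glucose concentrations following a 75-g OGTT at 28" weeks.

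Two of the three covariates are the stratification factors. The Randomisation procedure section says "Randomisation will be stratified by site to ensure balanced allocation of participants across the two arms at each of the three sites". It names ethnicity as the other factor. The third covariate, preconception glycaemia, comes from the baseline OGTT and is the baseline form of the outcome.

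The Background names the risk factors at issue: "Established risk factors for developing GDM include prepregnancy obesity [25], excessive gestational weight gain [26], advanced maternal age [27"; the same sentence ends with a previous pregnancy affected by GDM. The Trial design section places the physical measurements before allocation: "body anthropometry and metabolic phenotype ascertained and biosampling undertaken, followed by randomisation". Age is an entry criterion. The legend to Fig. 1 lists medical-history and obstetric-history questionnaires.

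Under Power calculations the plan expects losses between randomisation and analysis. From as many as 900 women per arm, "a total of 600 pregnancies and 500 live births is conservatively anticipated".

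**The concern.** The protocol gives its own reason for adjusting: the women who reach 28 weeks may not be balanced between arms, although the women randomised were. The reason is sound. The analysed set is a minority of those randomised, and it is formed by conceiving, staying pregnant and staying in the study, all after the drinks have started. A model chosen for that reason would be expected to include the baseline factors most likely to matter for glucose in pregnancy.

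The protocol names three such factors that exist before randomisation: obesity, age and previous GDM. It uses none of them. Gestational weight gain, which the same sentence names, is rightly absent because it arises after randomisation.

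At stake are two modest things. An imbalance in BMI, age or previous GDM would move the estimate to the extent that preconception glucose does not already account for it, and the target fasting effect is small. Leaving out prognostic baseline variables also gives a slightly wider confidence interval than the collected data allow.

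**Working it through.** **Fraction analysed.** With up to 900 per arm, 1,800 women are randomised.
- 250 per arm with OGTT data: 500/1800 = 27.8%.
- 300 per arm: 600/1800 = 33.3%.

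**Implied SD.** The protocol states no SD, so its power figures cannot be reproduced directly. I solved for the SD that they imply (two-sided test, normal approximation, 1:1 allocation):

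SD = delta / [(z for alpha + z for power) x sqrt(2/n)]

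- Fasting (0.1 mmol/L, 89% power, 5% level, 250 per arm): 0.1 / [(1.960 + 1.227) x 0.0894] = 0.351 mmol/L. The standard error of the difference is 0.351 x 0.0894 = 0.031 mmol/L.
- 2-h (0.3 mmol/L, 84%): SD 1.135.
- 60-min (0.43 mmol/L, 80%): SD 1.716.

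**Assumption.** The documents give no R2 for BMI, age or previous GDM. I assume that together they explain 3-10% of the variance left after site, ethnicity and preconception glucose, and I treat them as one combined score. I take 0.351 as the residual SD; if it is an unadjusted SD, the shifts below are somewhat too large.

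**Shift from a chance imbalance at its 95% limit.** With 250 per arm, a standardised baseline difference has SD sqrt(2/250) = 0.0894, so its 95% limit is 1.96 x 0.0894 = 0.175.

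Shift in the fasting difference = sqrt(R2) x 0.351 x 0.175

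| Assumed R2 | Shift (mmol/L) | Share of the 0.1 target |
|---|---|---|
| 3% | 0.011 | 11% |
| 5% | 0.014 | 14% |
| 10% | 0.019 | 19% |

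In standard errors, the shift is 1.96 x sqrt(R2), or about 0.3 to 0.6.

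**Check against the other power statement.** The statement for 300 per arm (0.12 mmol/L fasting, 80% power, alpha 0.017) implies a fasting SD of 0.455. The shift is then 0.013-0.023 mmol/L for R2 of 3-10%, which is 11-19% of 0.12. The share of the target hardly depends on which statement is used.

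**Precision.** Adding the covariates multiplies the standard error by sqrt(1 - R2), which is equivalent to 250/(1 - R2) women per arm.

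| Assumed R2 | Equivalent n per arm | Power: fasting / 2-h / 60-min |
|---|---|---|
| 0% (stated) | 250 | 89 / 84 / 80% |
| 3% | 258 | 89.9 / 85.1 / 81.2% |
| 5% | 263 | 90.5 / 85.8 / 82.0% |
| 10% | 278 | 91.9 / 87.6 / 84.0% |

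The gain is worth about 8-28 women per arm, and at most about 3-4 points of power.

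**Whether the protocol already covers this.** The sensitivity analyses under Statistical analysis omit groups of participants, change the analysis set, drop outliers or impute missing data. None adds covariates to the treatment comparison. The planned prognostic models of the primary outcome use baseline covariates, but they are not described as part of that comparison.

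**The case against.** The strongest reply is that the chosen set is standard: both stratification factors plus the baseline measure of the outcome. The sentence speaks of accounting for potential imbalance and does not promise to remove all of it. The Background lists risk factors for GDM, which is a secondary, binary outcome, and gives no evidence that they predict 28-week glucose beyond preconception glucose. The SAP, which is not shown, may contain a model with more covariates. More than half of the participants had been recruited when the article was written.

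Much of this stands. The set is defensible, and nothing in the protocol contradicts it. How much the three factors add beyond baseline glucose is an assumption here. Still, GDM is defined in the same section by cut-offs on the same three OGTT readings, so risk factors for it are natural candidates. The covariate list is fixed in the protocol itself, so an SAP that follows it inherits the choice. The stage of recruitment is no obstacle while the data remain blinded.

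Three stronger readings are tempting, and the documents do not support them.
- **That imbalance in these factors goes uncorrected.** Whatever part of their effect already shows in preconception glucose is adjusted for.
- **That the estimate is biased.** Chance imbalance is sampling variation and is already in the standard error. Systematic imbalance would require the drink to affect who conceives, reaches 28 weeks or stays in the study, and the documents do not show this.
- **That the shift could reach about a third of the target.** A BMI SD of 6 kg/m2 with a slope of 0.03 mmol/L per kg/m2 would give 1.96 x 6 x 0.0894 x 0.03 = 0.032 mmol/L. But BMI alone would then explain (6 x 0.03)^2 / 0.351^2 = 0.0324/0.123, about 26% of fasting variance, which is far outside the 3-10% assumed here.

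**Conclusion.** The point holds as an improvement to a defensible model, not as an error. BMI, age and previous GDM are named as risk factors in the protocol's own Background and are left out of a model whose stated purpose is to deal with imbalance in the analysed pregnancies.

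At an assumed R2 of 3-10%, the consequence is modest: a possible shift of roughly a tenth to a fifth of the fasting target at the 95% limit of chance imbalance, and a small gain in precision. No planned power is lost, because the power section does not credit any covariate adjustment. If selection into the 28-week set did differ by arm, the extra covariates would reduce the resulting distortion but would not cure it.

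**What to change.** Before unblinding, specify in the protocol and SAP that the primary analysis of each glucose reading is a linear regression adjusting for:
- site and ethnicity;
- the corresponding preconception glucose value;
- preconception BMI and age, both continuous;
- previous GDM (yes / no / no previous pregnancy), where it is recorded before randomisation. The legend to Fig. 1 lists the history questionnaires, but their timing cannot be seen in the text available.

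Keep the three-covariate model as a supporting analysis. Do not add gestational weight gain or any other variable that arises after randomisation.

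The cost is one sentence, about four more parameters on about 500 women, and a simple stated rule for missing baseline values, such as mean imputation. Anthropometry and age are already collected. Specifying the covariates now also matters because adding BMI after an imbalance has been seen would look driven by the data.
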